#### Quality assurance of acupuncture treatment

EA and SA will be performed by acupuncturists licensed to practice traditional Chinese medicine with at least 5 years of clinical experience. Before the trial, all acupuncturists will be trained by the principle investigator (Doctor [name]) on all details of the acupoints, insertion depth, and manipulation methods.

#### Interventions

In the EA group, the acupoints of the bilateral Zhong Liao (BL33), Hui Yang (BL35), and San Yinjiao (SP6) will be stimulated using needles with sizes of 0.30 × 75 mm and 0.30 × 40 mm, whereas in the SA group, sham Zhong Liao (BL33), Huiyang (BL35), and San Yinjiao (SP6) will be stimulated using needles with sizes of 0.30 × 40 mm (Details in Table 2).

**Table 2 Tab2:** Details of interventions

		EA Group	SA Group
Retention time		30 min	
Treatment sessions		36 sessions	
Frequency and duration of treatment		3 sessions per week (every other day ideally) for 12 week	
Type of tools		SDZ-V electronic apparatus and Huatuo Brand disposable sterilized needles	
The first Pair of acupoints	Names	Zhong Liao (BL33)	Sham Zhong Liao (BL33)
	Location	Third foramina sacralia posteriora	1cun (≈10 mm) horizontally outwardly lateral to Zhong Liao (BL33)
	Needle type	0.30 × 75 mm	0.30 × 40 mm
	Depth of insertion	60~70 mm	2-3 mm to stand still
	Response sought	De qi	No sensation of de qi
	Manipulating method	The needle will be penetrated into skin at the area 0.5-1 cm upside and outside away from Zhong Liao (BL33), inserted further at a degree of 45° inward and downward into the foramina and lifted, thrusted and thrilled gently and evenly for three times.	Without any manipulation
	Electric parameters	Continuous wave, 20 Hz, 2 mA–6.5 mA. Adjust from zero to the degree which patients can tolerate.	Continuous wave, 20 Hz, 0.1–0.3 mA.
The second pairof acupoints	Names	Hui Yang (BL35)	Sham Hui Yang (BL35)
	Location	0.5 cun (≈10 mm) lateral to coccyx end	1cun (≈10 mm) horizontally outwardly lateral to Hui Yang (BL35)
	Needle type	0.30 × 75 mm	0.30 × 40 mm
	Depth of insertion	60~70 mm	2-3 mm to stand still
	Response sought	De qi	No sensation of deqi
	Manipulating method	The needle will be penerated into the skin at the area right beside the coccyx end, inserted further outward and upward slightly and lifted, thrusted and thrilled gently and evenly for three times.	Without any manipulation
	Electric parameters	Continuous wave, 20 Hz, 2 mA–6.5 mA. Adjust from zero to the degree which patients can tolerate	Continuous wave, 20 Hz, 0.1–0.3 mA.
The third pair of acupoints	Names	San Yinjiao (SP6)	Sham San Yinjiao (SP6)
	Location	Posterior border of medial tibia, 3cun above medial malleolus tip	0.5cun (≈10 mm) horizontally behind San Yinjiao (SP6)
	Needle type	0.30 × 40 mm	0.30 × 40 mm
	Depth of insertion	25-30 mm	2-3 mm to stand still
	Response sought	De qi. Electricity-shock feelings should be avoided.	No sensation of deqi
	Manipulating method	The needle will be penetrated downward and lifted, thrusted and thrilled gently and evenly for three times.	No manipulation
	Electric parameters	Continuous wave, 20 Hz, 1–3.5 mA. Adjust from zero to the degree which patients can tolerate	Continuous wave, 20 Hz, 0.1–0.3 mA

#### Solifenacin treatment group

In the solifenacin treatment group, patients will take 5 mg solifenacin orally per day for a succession of 36 weeks.

The five-degree Patient Global Symptom Control (PGSC) [13] will be applied at weeks 4, 8, 12, 24, and 36 to assess whether urinary leakage is adequately controlled by solifenacin, with a score of 1 indicating strong disagreement and a score of 5 indicating strong agreement. Patients can continue with the current dose of solifenacin if they score 4 or 5, and the dose can be increased to 10 mg per day if they score 1–3 points. However, the final decision will be made by the doctors under comprehensive consideration of the PGSC score and side effects. Solifenacin can be discontinued at any time in the event of severe side effects. The dose changes, discontinuation, and side effects will be recorded clearly in the case report form (CRF).

#### Concomitant treatment

To avoid other influences on the function of the lower urinary tract and incontinence symptoms, patients will be recommended not to receive any other treatments. If used, the treatment or medication should be clearly recorded in the CRF.

### Measures

#### Outcome assessment

##### Primary outcome measure

The primary outcome is the change in UUI episodes during an average 24-h period at 12 weeks from the baseline (after the first treatment), recorded in a 3-day voiding dairy.

##### Secondary outcomes

UUI episodes, urinary frequency, urgency, nocturia, pad consumption, and volume drunk in an average 24-h period will be recorded in a 3-day voiding diary both during the treatment period (week 4, week 8, week 12) and the follow-up period (week 24, week 36). The 3-day voiding diary is a reliable, objective, and sensitive measurement recommended by EAU guidelines to monitor changes in incontinence. Urination, urgency, incontinence, drinking, and pads consumed are recorded. Urgency will be evaluated using the Patient Perception of Intensity of Urgency Scale (PPIUS), which is recommended by the European Medicines Agency [14]. Voiding at levels of 3 and 4 are regarded as urgency episodes [15], while levels 1 and 2 are regarded as normal or a strong desire to void [14].

In addition, the ICIQ SF and OAB-q SF scores will be applied as outcome measurements both during the treatment period (week 4, week 8, week 12) and follow-up period (week 24, week 36). The ICIQ SF is a questionnaire developed by the International Consultation on Incontinence [16] to evaluate the severity of incontinence and impact on QoL in the past 4 weeks. It contains four items: frequency, amount of leakage, impact of UI on QoL, and a separate item to indicate the cause of incontinence. The score is the sum of the first three items and the total score ranges from 0 to 21, with a higher score indicating worse symptoms and greater impact on QoL. A Chinese version has been translated and validated [17]. OAB-q SF is a validated questionnaire used to assess the burden of OAB symptoms and the effect on QoL in the past 4 weeks. The questionnaire includes items on coping, sleep, and emotional interactions [18]. The scores are transformed to a 0- to 100-point scale, with higher symptom-severity scores indicating worse symptoms and higher QoL scores indicating a better QoL. A Chinese version of OAB-q SF has also been validated [19].

Patient global impression improvement (PGI-I) will be applied in week 12 and week 36 to measure the effects of therapy subjectively. PGI-I is a scale ranging from 1 to 7, with 1 indicating very much better, 2 indicating much better up to 7 indicating very much worse [20].

Residual urinary volume will be retested with abdominal B-ultrasound in week 12 from the baseline.

The expectations of patients regarding acupuncture and Solifenacin will be assessed before the first treatment, and whether the patients in the EA and SA groups are blinded successfully will be assessed within 5 min after any treatment in the last week. Participants will be told that they may receive one of two treatments, traditional EA treatment, where traditional acupoints are inserted relatively deeply, or minimal EA treatment, where non-acupoints are inserted shallowly and gently. Then they will be asked to guess if they received traditional EA, and choose from answers of yes or no.

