#### Blinding

Patients will be informed that they might be allocated to one of the three groups before enrollment. Patients in the EA and SA groups will be unaware of the allocation while those in the solifenacin group will not be blinded. The procedures for SA will be identical to those for EA, except that needles will be inserted into non-acupoints shallowly, with no manipulation, no sensation of *deqi,* and a minimal electric current. Patients will be treated separately to prevent communication. After 12-week treatment, the blinding effect will be evaluated.

Except for the acupuncturists, the principal investigators, co-investigators, research assistants, outcome assessors, and statisticians will all be blinded to the allocation.

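### The blinding question describes the two needling techniques and may be asked before the week-12 diary and questionnaires are complete, so it can prompt EA and SA patients to infer their group while the primary outcome is still being recorded

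*Protocol article*

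**What the plan says.** Two places in the protocol article set the timing of the blinding check, and they differ.

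- **Secondary outcomes:** whether EA and SA patients are successfully blinded "will be assessed within 5 min after any treatment in the last week". With three sessions a week for 12 weeks (Table 2), this permits the check after session 34, 35 or 36.
- **Blinding:** "After 12-week treatment, the blinding effect will be evaluated". Read plainly, this is after treatment has ended.

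The Secondary outcomes section also fixes the content. Patients are told that they may have received either traditional EA, with fairly deep needling at acupoints, or "minimal EA treatment, where non-acupoints are inserted shallowly and gently". The guess comes second: "Then they will be asked to guess if they received traditional EA", answered yes or no.

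The primary outcome is stated as follows: "The primary outcome is the change in UUI episodes during an average 24-h period at 12 weeks from the baseline", taken from a 3-day voiding diary. The Abstract places it after the 12-week treatment. Table 1 lists the blinding evaluation at week 12, the same timepoint as the diary, ICIQ SF, OAB-q SF and PGI-I, and gives no order among them. The diary and both questionnaires recur at weeks 24 and 36, and PGI-I at week 36.

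On masking, the Blinding section says: "Patients in the EA and SA groups will be unaware of the allocation". Solifenacin patients are open-label and are not asked the question.

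**The concern.** The diary and the questionnaires are reported by the patients themselves, and EA versus SA is the only comparison in which patients are blinded. The prompt names the features on which the two techniques differ, minutes after a session, and then asks patients to classify themselves. Table 2 shows that the contrast is a physical one: insertion of 2–3 mm without deqi in SA, against 60–70 mm (BL33, BL35) or 25–30 mm (SP6) with deqi in EA.

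If the prompt comes before the week-12 diary is complete, some patients may record the primary outcome with a stronger belief about their group than they would otherwise have held. SA patients who conclude that they had the minimal version may report less improvement, and EA patients may report more. SA is the reference in both steps of the primary analysis (solifenacin versus SA for assay sensitivity, then the 50% retention test), so a change in SA reporting reaches both.

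**Working it through.** **1. Can the check precede the diary?** The article does not give calendar days, so the following is an illustration. Assume the first session is on day 1 and sessions fall on alternate days within each week. Week 12 then runs from day 78 (11 × 7 + 1) to day 84, with sessions 34, 35 and 36 on days 78, 80 and 82.

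| Assumed diary days | Check after session 34 (day 78) | After session 35 (day 80) | After session 36 (day 82) |
|---|---|---|---|
| 79–81 | before the diary | during the diary | after the diary |
| 82–84, ending at 12 weeks | before | before | during |
| 85–87, after the treatment week | before | before | before |

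The check follows the completed diary in only one of these arrangements. They are possibilities under the stated rules, not frequencies. If the check is instead made after treatment ends, as the Blinding section says, the order depends on when the diary is kept, and nothing requires the diary to come first. Under either timing, weeks 24 and 36 follow the check.

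**2. How would a reporting shift enter the primary analysis?** Let EA, Sol and SA be mean improvements, and D = Sol − SA. Statistical analysis requires EA − SA to exceed 0.5 × (Sol − SA), that is

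C = (EA − SA) − 0.5(Sol − SA) = EA − 0.5 Sol − 0.5 SA > 0.

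- If SA patients report b less improvement, C rises by 0.5b, because SA also stands in the comparator difference. The assay-sensitivity difference rises from D to D + b.
- If EA patients report a more improvement, C rises by a.

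**3. Sensitivity, with assumed values.** For true retention R = (EA − SA)/D and an SA shift b alone, the apparent retention is R′ = (R·D + b)/(D + b).

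| True R | b | R′ |
|---|---|---|
| 0.40 | 0.1D | 0.50/1.10 = 0.45 |
| 0.40 | 0.2D | 0.60/1.20 = 0.50 |
| 0.30 | 0.4D | 0.70/1.40 = 0.50 |

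From a true retention of 0.40, the average SA shift must reach 20% of the whole solifenacin–SA difference before apparent retention touches the 50% threshold. From 0.30 it must reach 40%. The article gives no value for a, b or D, so these rows show direction and sensitivity and estimate nothing.

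**4. Who is exposed?** At most 94 + 94 = 188 patients. That is an upper bound, reached only if every EA and SA patient is asked before finishing the diary.

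**The case against.** A reader might infer that the check hands patients the key to their allocation and so unblinds them, or that EA minus SA is necessarily biased upwards. The documents do not support either, for these reasons:

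- **Consent.** Study design says that patients are informed of the study's details, and the paragraph on consent goes on to describe SA as shallow, minimal EA at non-acupoints, much as the prompt does. The consent form is not shown. If it carries this description, the prompt reveals little that is new.
- **Wording.** The prompt speaks of minimal EA, not sham. It gives no depths in millimetres, and no feedback on the guess is described. Patients are treated separately and have felt only one technique.
- **Prior exposure.** The sensory contrast has been present through at least 11 × 3 = 33 sessions before week 12, so much of any unblinding it causes would predate the check.
- **Dilution.** An SA shift moves the retention criterion by only half its size.
- **Later outcomes.** Analyses other than the primary are declared descriptive, so exposure at weeks 24 and 36 matters less.

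All of this stands and limits the likely size. It does not remove the problem of order: repeating the description just after a session and asking for a self-classification is a fresh cue, whatever patients were told at consent.

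Two further objections stand only in part. ICIQ SF and OAB-q SF look back over 4 weeks, so the prompt touches little of that window; but the answers are given when the form is completed, which may be after the prompt. The sequence of assessments within a visit is often left to a fuller protocol or the CRF; here, however, the article itself fixes a timing rule and a script, and its two timing statements disagree.

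**Conclusion.** The point holds as a cheap improvement to the conduct of the blinding check. The article's timing rule lets a descriptive prompt reach EA and SA patients before or during the primary 3-day diary, and its two statements on timing need reconciling. The likely direction favours EA over SA. The size is unknown and may be small. It depends on how many patients are asked before the diary is complete, what the consent form already tells them, and how far a changed belief alters diary entries; the article gives none of these. The text does not show that the check will unblind patients or that the primary comparison is biased, only that an avoidable route to such bias has been left open in the one patient-blinded contrast.

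**What to change.** Reconcile the Blinding and Secondary outcomes sections, and state that the blinding question is asked only after the week-12 diary, ICIQ SF, OAB-q SF and PGI-I have been collected. This needs one CRF instruction and a memo to sites. Sample size, treatment and analysis are unchanged. Recruitment has already started, so an early change protects more patients. The downside is small: the guess is no longer taken within 5 minutes of a session.

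Two further changes are optional. Less descriptive wording would limit cueing before the week-24 and week-36 outcomes, although patients may find a question without any description harder to answer, since both arms receive electroacupuncture. A *do not know* response would let uncertainty be recorded. Both are matters of preference, and the main fix does not depend on them.

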#### Safety assessment

##### Side effects associated with acupuncture

Unintended events and feelings related to EA and SA will be recorded in the CRF, including broken needles, fainting, bleeding, bruising, infection and aposteme, unbearable ache (VAS ≥ 8), vomiting, nausea, palpitations, dizziness, headache, anorexia, and insomnia.

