## Methods and analysis

### Study design

The study will be a multicentered, randomized, three-armed, non-inferiority clinical trial with sham electroacupuncture (SA) and solifenacin as controls. The null hypothesis is that the improvement (difference in the number of UUI episodes between baseline and 12-week assessment) in the EA group would be 50% or less of the difference in improvement between the solifenacin and SA groups; that is, noninferiority would be established if EA, compared with solifenacin, retains at least 50% of the efficacy of solifenacin over SA. The outcome assessors and statisticians will be blinded. Patients in the EA and SA groups will be blinded, while those in the solifenacin group will not be blinded. The study will be carried out after the ethics is approved by the Institutional Review Board. All the patients in the study will be informed about the details of the study and written informed consent will be obtained before enrollment.

In the written informed consent, the participants will be informed that if they are eligible and willing to participate in the study, they will be randomized into the EA group, SA group, or solifenacin group with the same probability. The investigators plan to enroll 282 participants, with 94 in each group. Solifenacin is an effective treatment for the UUI component, as recommended by the current guidelines, and our previous studies indicated that EA and SA are both effective for urgency-predominant MUI to some degree. In the EA group, participants will receive traditional EA at traditional acupoints, while participants in the SA group will receive shallow and minimal EA at non-acupoints.

The study is designed and reported in accordance with the Consolidated Standards of Reporting Trials (CONSORT) guidelines, the Standard Protocol Items: Recommendations for Interventional Trials (SPIRIT) Checklist, and Standards for Reporting Interventions in Controlled Trials of Acupuncture (STRICTA) recommendations. The protocol has been reviewed, revised, and supported by experts in statistics, urology, and acupuncture.

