##### Side effects associated with solifenacin

The side effects induced by Solifenacin will be recorded in the CRF, including dry mouth, dry eyes, and constipation.

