##### Adverse events

Except from the side effects induced by EA, SA, and solifenacin, all other adverse events will be recorded in the CRF throughout the trial, and their relationships with the intervention and controls will be assessed.

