### Statistical analysis

For the primary hypothesis, we will compare the decrease in UUI episodes among the three groups. A decrease in number will indicate less incontinence. Additionally, we will use a modified *t*-test based on the retention of effect method to analyze whether EA is noninferior to solifenacin [21]. In detail, to establish the assay sensitivity of the trial, a *t*-test investigating the superiority of solifenacin over SA will be performed first by comparing the decrease in the number of UUI episodes in the solifenacin and SA groups. After superiority has been established, a modified *t*-test will be used to assess whether the difference in the numbers between the EA and SA groups is more than 50% of the mean difference between the numbers in the solifenacin and SA groups. An appropriate Fieller’s confidence interval can also be provided [21]. If the *P* Value is equal to or less than 0.025 or if the lower boundary of the confidence interval around the mean difference between the numbers in the EA group versus that in the solifenacin group exceeds this value, then noninferiority will be established. After the noninferiority assessment, traditional *t*-tests will be used for superiority analyses, including a decrease in the number of UUI episodes for solifenacin versus EA, and EA versus SA.

A mixed-effect model or Wilcoxon rank-sum test will be used to assess the longitudinal continuous variables. A generalized linear model or logistic regression will be performed to assess the rates of response. Chi-square or Fisher’s exact tests will be used to compare the frequency of AEs between groups.

Primary outcome analysis will be performed in the intention-to-treat (ITT, randomized participants) and per-protocol datasets (PP, ITT participants who received at least one treatment session without major violation of the protocol). Missing data will be imputed using the multiple imputation method under the missing-at random assumption. Secondary and safety outcomes will be assessed in ITT populations.

Since all analyses other than the primary analysis are considered descriptive, no adjustments will be made for multiple testing, and *P* values should be interpreted accordingly. Analyses will be performed using SAS version 9.4 (SAS Institute Inc) with a two-sided *P* value of less than .05 considered significant.

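### Needling pain is named as an acupuncture side effect only at VAS 8 or more, while solifenacin side effects carry no severity cut-off, so the between-arm harm comparison can under-count unintended EA pain

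*Protocol article*

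**What the plan says.** All places are in the protocol article.

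- **Side effects associated with acupuncture.** The section opens with a general rule followed by examples: "Unintended events and feelings related to EA and SA will be recorded in the CRF, including broken needles, fainting, bleeding, bruising". Pain appears among the examples only as "unbearable ache (VAS ≥ 8". None of the other items, such as bruising, nausea, dizziness or headache, has a severity threshold.
- **Side effects associated with solifenacin.** "The side effects induced by Solifenacin will be recorded in the CRF, including dry mouth, dry eyes, and constipation". No severity threshold is stated.
- **Adverse events.** The catch-all reads "Except from the side effects induced by EA, SA, and solifenacin, all other adverse events will be recorded in the CRF throughout the trial".
- **Statistical analysis.** "Chi-square or Fisher’s exact tests will be used to compare the frequency of AEs between groups". The same section treats everything except the primary analysis as descriptive.
- **Interventions, Table 2.** EA needles go in 60 to 70 mm at BL33 and BL35 with manipulation, and the EA current follows the instruction "Adjust from zero to the degree which patients can tolerate". SA uses 2 to 3 mm, no manipulation and 0.1 to 0.3 mA.

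**The concern.** The expected complaints of one treatment appear to count at any grade, while the expected pain of the other is named only near the top of the scale. If centres follow the list literally, a woman with unintended needling pain of 5 or 6 contributes no event, whereas a woman with mild dry mouth contributes one. The frequencies then tested would not measure the same thing in each arm.

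The cut-off falls most heavily on EA. A current raised to what the patient tolerates should keep most pain short of unbearable, which is the range the list does not name. The EA versus SA contrast uses one definition, but it could still miss an excess of moderate pain with the deeper and stronger EA.

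Tolerability is part of the case for EA: the Background cites the common side effects of solifenacin and its high discontinuation rate, and asks for alternatives with better effectiveness and safety. A tilted count would support that argument for the wrong reason.

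**Working it through.** The plan states no pain or side-effect rate, so it has no figure to reproduce. The check is mainly textual, with an illustration.

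**Step 1. Is the cut-off specific to pain?** The acupuncture list has 13 items: broken needles, fainting, bleeding, bruising, infection and aposteme, ache, vomiting, nausea, palpitations, dizziness, headache, anorexia and insomnia. One of the 13, ache, has a numeric cut-off. The three named solifenacin effects have none.

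**Step 2. Is pain below 8 picked up elsewhere?** There are two routes.
- The general clause on unintended feelings could cover it, because the list is introduced as examples. But a stated threshold has a purpose only if pain below it is not counted.
- The catch-all excepts side effects induced by EA and SA. Pain caused by needling is such a side effect, so it is not clearly recovered there.

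Pain below 8 is therefore neither plainly recorded nor plainly excluded.

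**Step 3. Does it reach an analysis?** Chi-square or Fisher's exact tests "will be used to compare the frequency of AEs between groups". I assume that AEs here include the listed side effects; the catch-all's reference to other adverse events suggests so.

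**Step 4. Illustration.** The arm size comes from Study design: "The investigators plan to enroll 282 participants, with 94 in each group". Every rate below is an assumption.

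Women with unintended needling pain = 94 × rate. Women counted = 94 × rate × share reaching VAS 8. Results are rounded to whole women.

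| Assumed pain rate | Women with pain | Counted, 10% reach VAS 8 | Counted, 25% | Counted, 50% |
|---|---|---|---|---|
| 10% | 94 × 0.10 = 9.4, about 9 | 1 | 2 | 5 |
| 20% | 94 × 0.20 = 18.8, about 19 | 2 | 5 | 9 |
| 40% | 94 × 0.40 = 37.6, about 38 | 4 | 9 | 19 |

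Now suppose that solifenacin side effects also affect 20% of women (19 of 94) and are all counted. The two-sided Fisher's exact test of solifenacin versus EA, on these events alone, gives:

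| Share of EA pain reaching VAS 8 | Solifenacin v EA, counted | p |
|---|---|---|
| All pain counted | 19 v 19 | 1.0 |
| 50% | 19 v 9 | 0.06 |
| 25% | 19 v 5 | 0.004 |
| 10% | 19 v 2 | 0.0001 |

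Under these inputs the cut-off alone can turn an equal burden into an apparent advantage for EA. The table shows the mechanism and does not estimate the effect in this trial. It also leaves out every other EA event.

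**The case against.** The strongest defence has five parts.

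- **The list is open.** Unintended feelings are to be recorded, and the VAS item is one example. This stands. A reader might infer that the plan forbids recording pain below 8, or that most EA pain is lost; the text says neither. What remains is that the threshold invites that practice, and six hospitals could read it differently.
- **One item of 13 is affected.** This also stands. Trivial bruising or bleeding counts against EA, so it would be wrong to describe the whole comparison as any-grade drug effects against extreme-grade needling effects. Counting solifenacin effects at any grade is itself inferred from the absence of a cut-off, and the full protocol or CRF may grade them.
- **A threshold has a reason.** Deqi is the response sought, and strong local sensation is intended. That justifies separating intended sensation from harm. It does not explain leaving unintended pain below 8 unnamed.
- **The rates have no source.** Correct. No claim about how much pain is missed can be drawn from the document, and the p-values above follow from the chosen inputs.
- **Safety is descriptive.** Correct: no safety hypothesis is formally tested, and the noninferiority question concerns UUI episodes. Harm rates will nevertheless be compared by arm, and unequal counting misleads whether or not the comparison is confirmatory.

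The article condenses a fuller protocol, but the point is about a criterion that the article states, not about detail left out.

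**Conclusion.** The point holds in a limited form. As written, the recording rule names needling pain only at VAS 8 or more and sets no cut-off for solifenacin side effects, and the catch-all does not clearly close the gap. Applied literally, it can under-count unintended EA pain relative to solifenacin, and possibly relative to SA, in the AE comparison.

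The likely direction, in favour of EA, rests on two assumptions: that centres treat VAS 8 as a reporting threshold, and that solifenacin effects are recorded at any grade. The size is unknown, because the document gives neither a pain rate nor a distribution of scores. A reader might go further and infer that EA's pain is largely removed from the comparison, or that the trial's main conclusion is compromised. Neither is supported: the first needs rates that are not given, and the primary efficacy analysis does not use these data.

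**What to change.** In the section on acupuncture side effects, record unintended needling pain with its VAS score whatever the score, and keep VAS 8 or more as the severe category. Define unintended pain as distinct from the sought deqi sensation, for example pain that the patient reports as a side effect or that persists after the session. A rule that counted any VAS above 0 without this distinction could turn routine insertion or deqi into an adverse event and bias the comparison the other way.

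Grade solifenacin side effects as mild, moderate or severe too. Report the between-arm comparison at any grade and at moderate or worse, with the same categories in all three arms. Fix the VAS band for moderate pain before the comparison is made; the document gives only the boundary at 8.

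The cost is one extra CRF field and a higher reported EA side-effect rate. Recruitment has already started, so pain below VAS 8 may be unavailable for women already treated; the report should disclose this.
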